### Control group

Women in the control group will receive usual care during chemotherapy, which includes referral to a dietitian when malnutrition is detected by the gynaecological oncologist. Usual care does not include structured exercise and/or dietary counselling. To prevent non-participation and dropout, patients in the control group are offered a maximum of three exercise and three dietary counselling sessions in 12 weeks after completion of chemotherapy and the first follow-up measurement.

### Outcome measurements

An investigator blinded from group allocation conducts measurements at three time points. Participants are instructed not to reveal their group allocation. Baseline measurements are conducted before randomisation and at the start of chemotherapy (T0), the second measurement at 3 weeks after completion of chemotherapy (T1) and the last measurement (T2) at 12 weeks after T1. An overview of all outcome measurements is presented in table 3.

**Table 3 T3:** Summary of outcome measurements

Outcome	Instrument	T0	T1	T2
Primary outcomes				
Body composition	CT imaging for the assessment of skeletal muscle area	X	X	
	Bioelectric impedance analysis for the assessment of fat mass	X	X	X
Physical fatigue	Multidimensional Fatigue Inventory^64^	X	X	X
Physical function	European Organisation for Research and Treatment of Cancer Quality of Life Questionnaire Core 30^63^	X	X	X
Secondary outcomes				
Physical activity	Accelerometer (actigraph) for objective measurement of physical activity in 7 consecutive days during all waking hours	X	X	X
	Physical Activity Scale for the Elderly^78^ for self-reported levels of physical activity	X	X	X
Physical fitness	Maximum oxygen uptake (peak VO_2_) during a maximum exercise test on a cycle ergometer using a ramp protocol for the assessment of cardiorespiratory fitness	X	X	X
	Handheld dynamometer for the assessment of muscle strength	X	X	X
Body mass index	Body height on a calibrated scale to the nearest 0.1 mm	X	X	X
	Body weight on a calibrated scale to the nearest 0.1 kg	X	X	X
Dietary intake; WCRF/AICR guidelines	Food frequency questionnaire (developed by Wageningen University)	X	X	X
Dietary intake; protein intake	Self-composed food frequency questionnaire	X	X	X
Health-related quality of life and symptoms	European Organisation for Research and Treatment of Cancer Quality of Life Questionnaire–Ovarian Cancer Module 28^79^	X	X	X
	European Organisation for Research and Treatment of Cancer Quality of Life questionnaire–Chemotherapy-Induced Peripheral Neuropathy 20-Item Scale^80^	X	X	X
	Hospital Anxiety and Depression Scale^81^	X	X	X
	Pittsburgh Sleep Quality Index^82^	X	X	X
Chemotherapy therapy completion rates and treatment toxicity	Medical records of which chemotherapy completion rates will be assessed as the relative dose intensity, that is, the amount of particular chemotherapy given in relation to the originally planned chemotherapy dose		X	
Other study parameters				
Blood sampling	Venous blood sample (40 mL)	X	X	
Smoking and sociodemographics	Self-composed questionnaire	X		
Contamination of control group*	Self-composed questionnaire		X	

*Parameter will only be assessed in the control group.

AICR, American Institute for Cancer Research; WCRF, World Cancer Research Fund.

### Primary outcomes

Primary outcomes are body composition, physical function and fatigue. The body composition is assessed via skeletal muscle area and fat mass. The skeletal muscle area is assessed at T0 and T1 using routine CT imaging (first image extending from the third lumbar vertebra to iliac crest) conducted for diagnostic purposes. CT is considered the gold standard for assessment of muscle mass in patients with cancer.^60^ Because the CT of the third lumbar vertebra is not yet validated for the assessment of body fat mass,^61^ fat mass is assessed with a non-invasive measurement BIA.^62^ Physical function is assessed using the physical function subscale of the validated European Organisation for Research and Treatment of Cancer Quality of Life Questionnaire Core 30.^63^ Physical fatigue is assessed with the physical fatigue subscale of the Multidimensional Fatigue Inventory.^64^

### Secondary outcomes

Secondary outcomes are physical activity, physical fitness (ie, cardiorespiratory fitness and muscle strength), dietary intake, BMI, health-related quality of life and symptoms of neuropathy, anxiety and depression, sleep disturbances, chemotherapy treatment toxicity and completion rates. The measurement instruments for the assessment of the secondary outcomes are presented in table 3.

### Other study parameters

During the T0 and T1 visit, a venous blood sample is drawn and stored in the PADOVA biobank for future biomarker studies (eg, to assess immune system functioning). Because collection of blood samples is an addition to participation in the PADOVA study, an additional informed consent is obtained. Covariates such as clinical data (eg, cancer subtype, FIGO stage) and sociodemographic characteristics (eg, age, ethnicity) are assessed at baseline. Contamination (ie, received supervised exercise and/or dietary counselling) of the control group is assessed by a questionnaire at T1.

### Process evaluation

A process evaluation is conducted using a mixed-methods approach (using both quantitative and qualitative research methods). Quantitative data on behavioural counselling skills of dietitians are assessed during counselling sessions with the Behaviour Change Counselling Inventory.^65^ Patients in the intervention group fill out the Health Care Climate Questionnaire to assess the extent to which they perceive an autonomy-supportive environment during counselling.^66^ Quantitative data on behavioural determinants of physical activity and dietary behaviour (ie, outcome expectations, self-efficacy for eating and exercise habits, sociostructural factors, stage of change, type of motivation and knowledge) are assessed on T0, T1 and T2 by questionnaires in all patients. The following process evaluation components are examined by physical therapists and dietitians and reported in a form: dose delivered, dose received and fidelity. Acceptability of the intervention is assessed by a questionnaire filled out by patients and semistructured interviews among patients, physical therapists and dietitians conducted by a researcher. Interviews will be transcribed verbatim, coded in several phases^67 68^ and analysed with Atlas.ti 8.4.20. Analyses are partly performed concurrently with data collection because interviews will be held until data saturation is reached. An overview of all measurement instruments for process evaluation is presented in table 4.

**Table 4 T4:** Overview of all measurement instruments for process evaluation

Outcome	Instrument	T0	T1	T2
Process evaluation				
Behavioural determinants	Multidimensional Outcome Expectations for Exercise Scale^78^	X	X	X
	Self-efficacy for eating and exercise habits—self-composed items	X	X	X
	Sociostructural factors, self-composed items	X	X	X
	Stage of change^83^	X	X	X
	Type of motivation: Treatment Self-Regulation Questionnaire^84^	X	X	X
	Knowledge (on WCRF recommendations): Items used in previous study^85^	X	X	X
Acceptability of intervention	Self-composed items*		X	
	The Healthcare Climate Questionnaire–Short Form (six items)^66^		X	
Acceptability of intervention	Semistructured interviews in healthcare professionals†		X*	X‡
	Semistructured interviews in participants		X*	X‡
Dose delivered	Checklist†—Amount of (components of) sessions provided by physical therapist/dietitian	Daily, during intervention		
Dose received	Checklist†—Amount of (components of) sessions participants actively engaged in	Daily, during intervention		
Fidelity	Checklist†—Extent to which the intervention was executed as prescribed in the protocol (eg, reasons for and amount of adaptations to the protocol)	Daily, during intervention		
Behavioural counselling skills§	Behaviour Change Counselling Inventory^65^	During intervention		

*Parameters will only be assessed in the intervention group.

†Parameter will be examined in physical therapists and dietitians.

‡Parameter will only be assessed in the control group.

§Parameter will be examined in dietitians.

WCRF, World Cancer Research Fund.

### Sample size calculation

Sample size calculation is based on the results of a previous RCT among patients with breast cancer that evaluated the effects of a combined aerobic and resistance exercise intervention (similar to the PADOVA study),^28^ a pilot study among patients with ovarian cancer that evaluated the feasibility of an exercise intervention^34^ and clinically relevant differences in body composition and peak oxygen uptake.^34 69–74^ With 53 patients per study-arm, we are able to detect a clinically relevant between-group difference in effects directly after intervention on physical function (10 points), physical fatigue (2.7 points), body composition (3% in percentage body fat and muscle mass) and 10%–15% difference in peak oxygen uptake (alpha=0.05; power=0.80). Taking into account a dropout of 15%, we aim to include 61 patients per group. Dropout rates are based on the 10%–15% dropout rates from previously conducted Dutch exercise trials in patients with cancer.^27 28 75^

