### Participants

The study aims to include 122 adult (aged ≥18 years) women who are scheduled for (neo)adjuvant first-line chemotherapy treatment for primary epithelial ovarian cancer. Patients are excluded from this study if they have had a prior cancer diagnosis within 5 years, are not able to perform basic activities of daily living, have a contraindication for exercise (eg, heart failure), have a cognitive disorder or severe emotional instability (eg, schizophrenia, Alzheimer), are unable to read and/or write Dutch, or have a life expectancy of less than 3 months.

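### At the planned 15% dropout, 61 patients per group leave about 52, not the 53 per arm on which the stated 80% power rests

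*Protocol article*

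**What the plan says.** The Sample size calculation section of the protocol article ties its power claim to a number per arm: "With 53 patients per study-arm, we are able to detect a clinically relevant between-group difference in effects directly after intervention", with "alpha=0.05; power=0.80". The differences listed are 10 points for physical function, 2.7 points for physical fatigue, 3% for body fat percentage and muscle mass, and 10% to 15% for peak oxygen uptake. The next sentence sets the recruitment target: "Taking into account a dropout of 15%, we aim to include 61 patients per group". The source of the 15% follows: "Dropout rates are based on the 10%–15% dropout rates from previously conducted Dutch exercise trials in patients with cancer". The Participants section carries the target forward as a total: "The study aims to include 122 adult (aged ≥18 years) women".

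The section gives no inflation formula, no standard deviations and no sidedness for alpha. It does not say which outcome fixed the 53, or whether the 53 already allows for baseline adjustment.

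**The concern.** The 53 is the number per arm behind the power claim, and the 61 is meant to protect that number against a 15% loss. Dropout of 15% means 15% of the patients included, so the check is whether 85% of 61 is at least 53. It is not.

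What is at stake is the accuracy of the stated basis for the sample size, which the results report is likely to repeat. Retention of exactly 85% would look as if it met the plan, yet it would leave fewer patients than the plan's own power statement requires.

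**Working it through.** **Inputs, all from the Sample size calculation section:** 53 per arm needed; 15% dropout; 61 per group to be included; alpha 0.05; power 0.80. The total of 122 in the Participants section is 2 × 61. The primary analysis is at T1 (Statistical analysis section), so dropout before T1 is what counts.

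**1. Reproducing the stated figure.** Multiplying, 53 × (1 + 0.15) = 60.95, which rounds up to 61 and matches exactly. The formula is inferred from this match.

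**2. The number needed to keep 53 after a 15% loss.** Dividing, 53/(1 − 0.15) = 62.35, so 63 per arm (126 in total). Rounding only the total gives 106/0.85 = 124.7, so 125. Rounding therefore does not explain 122.

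**3. What 61 per arm leaves.** 61 × 0.85 = 51.85 per arm, which is 53 − 51.85 = 1.15 short per arm, or 2.3 in total. In patients, an arm of 61 can lose 8 and keep 53, whereas 15% of 61 is 9.15.

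**4. The dropout that 61 can absorb.** 1 − 53/61 = 0.131, or 13.1%.

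**5. Effect on power.** With no standard deviations, the step from the listed differences to 53 cannot be reproduced. Assumption: 53 per arm gives exactly 80% power, two-sided, for the outcome that fixed the sample size. The implied standardised difference is then 0.549 (two-sample t test), or 0.544 by the normal approximation. With that difference held fixed:

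| Patients per arm | Power, t test | Power, normal approximation |
|---|---|---|
| 53 | 80.0% | 80.0% |
| 52 | 79.2% | 79.2% |
| 51.85 (expected at 15% dropout) | 79.1% | 79.1% |
| 51 | 78.4% | 78.5% |

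The expected loss is 80.0 − 79.1 = 0.9 percentage points. If alpha is one-sided, power at 51.85 per arm is 79.2% by the normal approximation, so sidedness hardly matters. At 10% dropout, 61 × 0.90 = 54.9 per arm remain and power is 81.4% (two-sided, normal approximation).

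**The case against.** **Dropout may be lower than 15%.** The 15% is the top of the cited 10% to 15% range, the Discussion expects dropout to be low, and 61 per arm keeps 53 at any rate up to 13.1%. That stands as a comment on likelihood. It does not reconcile the figures, because 15% is the article's own planning value and 61 is said to allow for it.

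**The planned analysis adjusts for baseline.** If the 53 came from an unadjusted comparison, a baseline–outcome correlation r reduces the residual variance by a factor of about 1 − r². Offsetting the shortfall needs r² of about 1 − 51.85/53 = 0.0217, so r of about 0.15. If the 53 already allows for adjustment, that offset has been used. The article does not say which, so the 79% is conditional on the stated assumption. Neither case makes 61 × 0.85 equal 53.

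**Power below 80% on every primary outcome.** A reader might infer this, because one number per arm and one power are given for all outcomes. The document does not support it. A single number for several outcomes is normally set by the most demanding one, and the others then have more than 80%. Exactly 80% on each would require every difference to stand in the same ratio to its standard deviation, and no standard deviations are given. The loss can be claimed only for the outcome that fixed the 53.

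**Conclusion.** The figures 53, 15% and 61, printed in adjacent sentences, cannot all hold. At 15% dropout about 52 patients per arm remain, not 53, and 63 per arm would have been needed. This depends on no assumption beyond reading dropout as a share of those included. That the target came from multiplying by 1.15 is a likely inference, not a stated fact.

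The size is minor: about 1 patient per arm, and about 0.9 points of power for the outcome that fixed the sample size. The power figure rests on 53 giving exactly 80% for that outcome in an unadjusted two-sided t test. A reader might conclude that the trial is materially underpowered or must enlarge its target. The figures do not support that: the loss is under one point and disappears at dropout of 13.1% or less, which lies inside the cited range.

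**What to change.** Restate the sentence on dropout in the Sample size calculation section. For example: including 61 patients per group (122 in total) retains 53 per arm if dropout before T1 does not exceed about 13%; at 15% dropout about 52 per arm remain, and power for the outcome that determined the sample size is about 79%. Name that outcome, and say that the 79% assumes 53 per arm gives exactly 80% in a two-sided test.

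The cost is one sentence and a stated power about one point less favourable. The recruitment target, design and analysis stay as they are, and no extra patients are needed.

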### Statistical analysis

The primary analysis focuses on the effects of the intervention directly after completion of chemotherapy (T1), since both the intervention and control groups have received counselling from a physical therapist and/or dietitian at follow-up (T2). Data will be analysed according to the intention-to-treat principle.

Intervention effects (at T1) will be assessed using linear regression analysis for continuous outcomes by regressing the intervention on post-test value (T1) of the outcome, adjusting for baseline values (T0). To examine whether intervention effects on body composition, physical function or fatigue are mediated by changes in physical activity and fitness, and/or diet, a series of regression analysis according to the product-of-coefficients test will be conducted.^76^ Potential effect modification by relevant demographic (eg, age) and clinical (eg, cancer stage, treatment regimen) variables will be explored by adding the variable and its interaction term with the intervention into the regression model.

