### Recruitment and randomisation

Patients are recruited from the Center of Gynaecologic Oncology Amsterdam (which is a collaboration of all gynaecological oncologists from Amsterdam UMC, Netherlands Cancer Institute/Antoni van Leeuwenhoek and affiliated peripheral hospitals) and Catharina hospital and its collaborating peripheral hospitals in the south of the Netherlands. After diagnosis and before the start of neoadjuvant chemotherapy (±2 weeks) or adjuvant chemotherapy (±4 weeks), the gynaecological oncologist informs patients about the PADOVA study during an outpatient clinic visit. Written informed consent is obtained from all patients prior to participation. After baseline measurement, participants are stratified by FIGO stage (low (I/II) vs high (III/IV stage) and chemotherapy regimen (primary surgery followed by chemotherapy vs neoadjuvant chemotherapy followed by interval debulking and adjuvant chemotherapy) and randomly allocated to either a combined exercise and dietary intervention or a usual care group. An independent researcher performs the randomisation using a table of random numbers in blocks of four generated by an independent statistician. Allocation sequence is concealed from the research and clinical staff. After randomisation, patients in both the intervention and control groups receive a brochure with general information on physical activity, diet and body weight recommendations for cancer survivors.^36^ These recommendations are not individualised or supervised. Patients who do not wish to participate in the study are invited to complete a single questionnaire examining relevant characteristics and reasons for declining participation to verify representativeness of the study population. See figure 1 for an overview of the study design and procedures.

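### The stated T1 model leaves out the stratification factors, FIGO stage and chemotherapy regimen; if they predict T1 beyond the baseline value, standard errors are somewhat too wide and some power is given up

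*Protocol article*

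**What the plan says.** Recruitment and randomisation: after the baseline measurement, "participants are stratified by FIGO stage (low (I/II) vs high (III/IV stage) and chemotherapy regimen", the second factor being primary surgery then chemotherapy versus neoadjuvant chemotherapy, interval debulking and adjuvant chemotherapy. Two binary factors make four strata. Allocation is done "using a table of random numbers in blocks of four generated by an independent statistician".

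Statistical analysis: the intervention effect at T1 on continuous outcomes comes from a linear regression described as "regressing the intervention on post-test value (T1) of the outcome, adjusting for baseline values (T0". Neither stratification factor appears in that sentence. They come back later in the section for a different purpose, effect modification: "clinical (eg, cancer stage, treatment regimen) variables will be explored by adding the variable and its interaction term with the intervention".

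Sample size calculation: "With 53 patients per study-arm", differences in "physical function (10 points), physical fatigue (2.7 points), body composition (3% in percentage body fat and muscle mass" are said to be detectable with "alpha=0.05; power=0.80". No standard deviation is given, and the sidedness of alpha is not stated.

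**The concern.** Blocked allocation within strata balances the arms on stage and regimen. Whatever part of the outcome variance these factors explain then largely drops out of the true sampling error of the treatment effect. A model without them still counts that part in its residual variance. The reported standard error then exceeds the true one, intervals are too wide, and the test rejects less often than its nominal level. The design has paid for precision that the analysis does not use.

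The effect arises only if the strata predict T1 after T0 has been taken into account. For regimen the article's own timeline makes this plausible. Under Outcome measurements, T0 is at the start of chemotherapy and T1 is 3 weeks after its completion. With primary surgery, the operation is already past at T0. With neoadjuvant chemotherapy, interval debulking falls between T0 and T1. The same T0 score for function, fatigue or fat mass is therefore taken at a different stage of treatment in each regimen. The argument is weaker for muscle area, because it is read from routine diagnostic CT, whose timing relative to surgery is not stated.

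**Working it through.** **Inputs from the protocol article.** Four strata and blocks of four (Recruitment and randomisation); 53 evaluable per arm, alpha 0.05, power 0.80, 15% dropout and 61 per group (Sample size calculation); model with arm and T0 value (Statistical analysis).

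**Assumptions.** Alpha is two-sided. Blocks run within strata. R2 is the share of the variance left after T0 adjustment that the strata explain. It is not in the article, so 0% to 20% is shown.

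**The plan's own figure.** The 53 per arm cannot be reproduced without a standard deviation. Solving backwards with the normal approximation:

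d = sqrt(2/53) × (1.960 + 0.842) = 0.544.

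This implies standard deviations of 18.4 points for function, 4.96 for fatigue and 5.5 for the 3% body-composition difference. The noncentrality is 0.544 × sqrt(53/2) = 2.80. Power is 80% at R2 = 0 by construction.

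**Formulas**, with exact balance within strata and r = sqrt(1 − R2):

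- reported SE / true SE without strata = 1/r
- type I error without strata = 2 × [1 − Φ(1.96/r)]
- power without strata = Φ((2.80 − 1.96)/r)
- power with strata = Φ(2.80/r − 1.96)

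| R2 (assumed) | SE too wide by | Type I error | Power without strata | Power with strata | Gain (points) |
|---|---|---|---|---|---|
| 0% | 0% | 5.0% | 80.0% | 80.0% | 0 |
| 5% | 2.6% | 4.4% | 80.6% | 82.0% | 1.4 |
| 10% | 5.4% | 3.9% | 81.3% | 84.0% | 2.7 |
| 20% | 11.8% | 2.8% | 82.7% | 87.9% | 5.3 |

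Worked example at R2 = 10%: r = 0.949; 1/r = 1.054; 1.96/0.949 = 2.07, which gives a two-sided 3.9%; Φ(0.842/0.949) = 81.3%; Φ(2.80/0.949 − 1.96) = 84.0%. Gains are taken before rounding.

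**Simulation check.** 122 patients, four strata with assumed shares, permuted blocks of four, 15% random dropout, assumed T0–T1 correlation 0.5, and 6,000 runs per scenario.

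| R2 | Reported SE / empirical SD, without strata | Type I error without / with strata | Power without / with strata |
|---|---|---|---|
| 0% | 0.197 / 0.200 | 5.1% / 5.2% | 78.3% / 78.1% |
| 5% | 0.197 / 0.193 | 4.4% / 4.8% | 78.4% / 80.4% |
| 10% | 0.197 / 0.190 | 4.2% / 5.2% | 78.6% / 81.1% |
| 20% | 0.197 / 0.178 | 3.0% / 4.6% | 79.4% / 85.5% |

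The direction agrees with the formula. Simulated power is just below 80% already at R2 = 0, because 122 × 0.85 = 103.7 leaves about 52 per arm rather than 53. The formula at 52 per arm gives 79.2%. That shortfall has nothing to do with the strata.

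**The case against.** The strongest reply is that a journal article condenses the protocol. Its sentence on the model does not say that T0 is the only covariate, and a fuller protocol or SAP, not shown here, may add the strata. This stands in part: nothing in the article rules the factors out, and if a fuller document includes them, only the article's sentence needs correcting. But the article does state a model, and it gives stage and regimen a different role, as exploratory effect modifiers. The stated model can therefore be assessed as written and improved.

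Second, nothing in the article links stage or regimen to function, fatigue, muscle area or fat mass, and any influence on T1 that passes through T0 is already absorbed by the T0 term. This stands. A reader might infer from the timeline that regimen strongly determines the outcomes. The timeline makes a residual effect plausible but gives no size. At R2 = 0 nothing is lost, and R2 may differ between outcomes.

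Third, the calibration formulas assume exact balance. Incomplete blocks and dropout weaken it. This also stands: at R2 = 10% the simulated excess in SE is 0.197/0.190, or 3.7%, rather than 5.4%, and at 20% it is 0.197/0.178, or 10.7%, rather than 11.8%. A separate simulation, also with assumed stratum shares, gave type I errors of 4.7%, 4.1% and 3.6% at 5%, 10% and 20%. The formula values are therefore nearer an upper limit on the miscalibration. The simulated power gains (2.0, 2.5 and 6.1 points) are similar to the formula's or slightly larger.

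**Conclusion.** The point holds as a conditional matter of efficiency and calibration, of modest weight. If the strata explain 0% to 20% of the variance left after T0, the stated model reports standard errors 0% to about 12% too wide, the type I error goes from 5% down to about 3%, and 0 to about 5 points of power are forgone. These figures rest on the assumed R2 range, a two-sided test, 53 per arm and the back-solved d of 0.544.

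Two stronger conclusions are tempting and not supported. A reader might infer that the treatment effect is biased or the test invalid. It is not: allocation balances the strata, and the error is on the conservative side. A reader might also infer that the omission leaves the trial underpowered. By the formula, power without the strata is 80% to 83%, so the loss is measured against a better model and not against the planned 80%.

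**What to change.** State the primary model as: T1 outcome = arm + T0 outcome + FIGO stage (I/II vs III/IV) + chemotherapy regimen, and use it for all continuous outcomes. Keep the interaction models as the separate exploratory analyses they already are. If a fuller protocol or SAP already includes the two factors, align the article's description with it.

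The cost is small. Both factors are recorded at randomisation, and with 106 evaluable patients the residual degrees of freedom go from 106 − 3 = 103 to 106 − 5 = 101. If the strata turn out to explain nothing, almost nothing is lost (simulated power 78.1% against 78.3%). The article says that inclusion was still under way, so the change can be fixed before analysis. A T0-by-regimen term is optional and not needed for this point.
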